## Abstract

**Background:**

Urinary tract infection (UTI) as the most common healthcare-associated infection accounts for up to 36% of all healthcare-associated infections. Catheter-associated urinary tract infection (CAUTI) accounts for up to 80% of these. In many instances indwelling urinary catheter (IDC) insertions may be unjustified or inappropriate, creating potentially avoidable and significant patient distress, embarrassment, discomfort, pain and activity restrictions, together with substantial care burden, costs and hospitalisation. Multifaceted interventions combining best practice guidelines with staff engagement, education and monitoring have been shown to be more effective in bringing about practice change than those that focus on a single intervention. This study builds on a nurse-led initiative that identified that significant benefits could be achieved through a systematic approach to implementation of evidence-based practice.

**Methods:**

The primary aim of the study is to reduce IDC usage rates by reducing inappropriate urinary catheterisation and duration of catheterisation. The study will employ a multiple pre-post control intervention design using a phased mixed method approach. A multifaceted intervention will be implemented and evaluated in four acute care hospitals in NSW, Australia. The study design is novel and strengthened by a phased approach across sites which allows for a built-in control mechanism and also reduces secular effects. Feedback of point prevalence data will be utilised to engage staff and improve compliance. Ward-based champions will help to steward the change and maintain focus.

**Discussion:**

This study will improve patient safety through implementation and robust evaluation of clinical practice and practice change. It is anticipated that it will contribute to a significant improvement in patient experiences and health care outcomes. The provision of baseline data will provide a platform from which to ensure ongoing improvement and normalisation of best practice. This study will add to the evidence base through enhancing understanding of interventions to reduce CAUTI and provides a prototype for other studies focussed on reduction of hospital acquired harms. Study findings will inform undergraduate and continuing education for health professionals.

**Trial registration:**

ACTRN12617000090314. Registered 17 January 2017. Retrospectively registered.

**Electronic supplementary material:**

The online version of this article (doi:10.1186/s12913-017-2268-2) contains supplementary material, which is available to authorized users.

## Background

Urinary tract infection (UTI) is considered the most common healthcare-associated infection (HAI) [1], accounting for up to 36% of all healthcare-associated infections (HAIs) [2]. Catheter-associated urinary tract infections (CAUTIs) represent the majority of UTIs (up to 67% of UTIs in all hospital inpatients [3], and up to 97% in ICUs [4]). Between 12 and 16% of hospitalised patients may receive a short term indwelling urinary catheter (IDC) [5], and many of these IDC insertions have been identified as unjustified or inappropriate [6]. CAUTI risk increases considerably with duration of catheterisation [7], and generates substantial care burden and significant hospitalisation costs, patient distress, embarrassment, discomfort, pain and activity restrictions [7–9]. A recent Australian study indicated that 1.7% of inpatients, hospitalised for > 48 h, contract a UTI, adding additional days (mean = 4) to their length of stay (LoS) [10].

CAUTI is possibly the most preventable HAI [11], with significant potential cost savings. According to Mitchell et al.’s (2016) [10] calculations, there are ~380,600 extra public hospital bed-days used each year in Australia due to healthcare-associated urinary tract infections (the majority being catheter-associated [3]). Umscheid et al. (2011) [11] estimate that each CAUTI costs between $1200 and $4700 USD. In the Australian setting, Jackson et al. (2011) estimated that the costs associated with a patient diagnosed with CAUTI are twice as much as a patient not affected by CAUTI [12].

### Preventing CAUTI

Worldwide, there has been renewed interest and research into reducing the incidence of CAUTI, especially in the USA, with the introduction of non-payment for ‘reasonably preventable’ hospital-acquired complications [13]. An integrative review by Meddings et al. (2014) [1] evaluated interventions up to October 2012 to reduce IDC usage and CAUTIs. Meddings et al. (2014) found that interventions to reduce inappropriate IDC use, and bundles of interventions focusing on reducing unnecessary catheter use and general infection control were successful in reducing catheter use [1]. A component common to most urinary catheter bundles is timely catheter removal [14–20]. Meddings et al. recognised the importance of addressing socioadaptive factors in successfully implementing interventions [1]. These socioadaptive factors have since been addressed in the USA with the Agency for Healthcare Research and Quality (AHRQ) Comprehensive Unit-based Safety Program (CUSP). In a national US study, Saint et al. implemented CUSP in 926 units, and found a significant reduction in catheter use and CAUTI in non-ICUs [19]. Clinician education about recommended practice is a key part of interventions to address catheter use and CAUTI; nine studies since the Meddings et al. 2014 integrative review implemented a hospital (or multi-hospital) intervention to reduce CAUTI, and all included some form of education [14, 17, 19, 21–27]. Indeed, a systematic review of interventions to reduce device-related infections found that all interventions had some form of education as a key component [28].

From evaluating the literature on hospital-wide and multi-hospital interventions designed to reduce urinary catheter use and CAUTI, a gap was identified in study design; all identified studies used a pre-post design, which does not account for secular trends.

Studies investigating use of IDCs and CAUTI have been lacking in the Australian context [29, 30]. Extant literature includes hospital-based rates of IDC usage and/or rates of CAUTI, with some discussion of documentation, appropriate indications for IDC, and staff knowledge. Wynne et al. (2014) [29] found a point prevalence of 12.4% of patients with IDC in situ, in a tertiary teaching hospital in Melbourne. This included an acute inpatient facility and a sub-acute aged care and rehabilitation service. Wynne et al.’s study did not report on the days IDC in situ or prevalence of CAUTI, and a differentiation between short-term and long-term IDC usage was not made. So et al. (2014) conducted a chart audit in a hospital in Sydney, finding catheter utilisation of 11%. A study of staff and patient knowledge of IDC usage in two general medical wards in a Melbourne hospital found that the mean time an IDC was in situ was 5.8 days, and that a physician’s awareness of IDC presence was significantly associated with a shorter time IDC in situ [31]. Giles et al. (2015), in a pilot study, found the prevalence of IDCs in two wards in an Australian hospital (urology ward = 25%; orthopaedic ward = 31%), and rate of CAUTI = 2.2% [32]. Giles et al. then went on to describe the development and pilot of a bundled approach to target IDC utilization and CAUTI, however results of the intervention were not reported. A large point prevalence study in six Australian hospitals by Gardner et al. (2014) found a CAUTI prevalence of 0.9%, and urinary catheter prevalence of 26.3% (88.7% of these being IDCs) [33].

The foregoing studies highlight a gap in knowledge in the Australian healthcare context, in that there have been no studies investigating the effects of an intervention on reducing IDC utilisation and CAUTI rates in an acute care setting.

A multifaceted evidence-based intervention was piloted in two wards in an acute care hospital in the Hunter New England Local Health District, leading to a 50% reduction in IDC insertions, significantly reduced IDC duration and number of patients treated for CAUTI [34].

Building from the positive results from the aforementioned pilot, the present study aims to implement and evaluate an intervention across four acute care hospitals in NSW, Australia. To control for secular trends, implementation of the intervention will be phased across the hospitals.

## Methods/Design

### Aims

The primary aim of the study is to reduce IDC usage rates by reducing inappropriate urinary catheterisation and duration of catheterisation.

The secondary aims of the study are to identify:The current inpatient indwelling urinary catheter usage rate and incidence of CAUTI;If the implementation and adherence to bundled catheter care (BCC) reduces IDC use and CAUTI;How effective BCC is in improving IDC-related outcomes;The barriers and enablers to successful implementation of BCC; andThe cost benefits of implementation.

### Design

The study will employ a multiple pre-post control intervention design using a phased mixed method approach (Fig. 1).

**Fig. 1 Fig1:**
[figure not shown]
Study Design. Data collection points are indicated with diamonds on timeline

Implementation of the intervention across four acute care hospitals will be staged, with multiple clusters in each of two implementation stages. Pre and post point prevalence data comparison will occur within all hospitals pre and post intervention, as well as between the two Health Districts as detailed in Fig. 1.

The staged implementation of the intervention allows for a control between the two Health Districts.

A mixed method design provides a platform to explore in-depth existing barriers and enablers related to implementing practice change. The sequential phased nature of the study ensures that the necessary evidence is available to inform the subsequent implementation phase of the study. The focus groups will identify barriers and enablers to implementation and uptake and will inform strategies to embed the intervention into normal practice. Questions in the focus groups will be informed by results from the point prevalence and clinician surveys.

The control will be usual urinary catheterisation practice, i.e., no intervention or implementation strategies. NSW Health evidence-based practice guidelines for “Adult Urethral Catheterisation for Acute Care Settings” [35], and local clinical practice guidelines for urinary catheterisation for each Health District are available for all clinicians, and can be accessed online.

The Clinical Excellence Commission (CEC), a corporation addressing patient safety and clinical quality in the NSW Health context, established a CAUTI project in 2014 to “help healthcare professionals in reducing the incidence of CAUTIs in acute care settings” [36]. A urinary catheterisation course on an online NSW Health learning platform also exists [37].

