### Setting

The intervention sites are four acute care hospitals from two Health Districts in NSW, Australia. Hospitals have been purposively selected, matched on total bed numbers, activity type and activity levels (See Table 1).

**Table 1 Tab1:** Setting

Health District	Facility	Beds
1	Hospital A	360
	Hospital B	260
	Total beds Health District 1 = 620	
2	Hospital C	549
	Hospital D	318
	Total beds Health District 2 = 867	

A key difference between the two health districts is the system used for medical health records: Health District 1 uses paper-based medical records, whereas Health District 2 uses electronic medical records. Data collection methods and training have been individualised to accommodate these differences.

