**Fig. 2 Fig2:**
[figure not shown]
Timeline of implementation components. The intervention commences with four weeks of intensive education. For the first two months, compliance audits are completed on a weekly basis, and then continue on a monthly basis for the remainder of the 6-month intervention period. Champion meetings will be held on a monthly basis throughout the intervention period

**Table 4 Tab4:** “No CAUTI” Implementation strategies summary based on TIDieR

Implementation Strategy	Rationale	Mode of delivery	Delivered by	Delivered to and where	When/how often
Education					
Train-the-trainer workshops	To prepare educators to present the “No CAUTI” bundle to ward-based staff, and to train educators to complete urinary catheterisation competency assessments	Face-to-face (group)	Clinical nurse consultant – urology	Nurse educators from across hospital	1x 2-3 h workshop at each facility at start of intervention
Ward in-services	To familiarise staff with “No CAUTI” bundle and nurse-initiated removal flowchart To identify champions in each ward	Face-to-face (group)	Nurse educators	Nurses and medical officers from all adult inpatient wards, OTs, and EDs	Minimum 1x 20 min in-service in each ward at start of intervention
Monitoring and feedback					
Compliance audits and feedback	To monitor compliance with “No CAUTI” bundle and provide strategies to support implementation	Individual patient audit, and feedback face-to-face (group) to clinicians	Champions (clinicians previously identified in in-services)	All inpatient wards	Weekly for first two months and then monthly for remaining 4 months of intervention period.
Feedback of point prevalence of IDC usage and CAUTI	To focus clinicians on targets and progress	Face-to-face (group) and email	Research project staff	All clinicians at a ward, facility, and district level	Baseline, 4 months, and 9 months
Resources					
“No CAUTI” bundle posters	Prompt awareness and better documentation	Documents displayed in wards	N/A (passive component)	Nurses and medical officers	Ongoing
“No CAUTI” bundle badges	Prompt awareness of intervention and identify ward champions	Worn by clinicians and champions	N/A (passive component)	Nurses and medical officers	Ongoing
Catheter insertion DVDs	Educate nurses about correct catheterisation processes	Available on intranet	N/A (passive component)	Nurses	Ongoing
Facilitation					

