### Statistical analysis – point prevalence data

Statistical analysis will be undertaken to determine differences in the prevalence of IDCs between Health District 1 (post) and Health District 2 (no intervention). A mixed methods analysis will compare pre and post data within the groups, across the time frame. Within group data will be stratified according to wards to allow for variation in the case mix of patients between wards. If differences in patient demographics are detected at baseline these will be controlled for in the between group analyses. Data linkage will be used to determine LoS and CAUTI rates for patients at each time point.

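### Staging by Health District gives one unit per stage, so the controlled contrast removes trends common to both districts but cannot separate the intervention from a change confined to one district

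*Protocol article*

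**What the plan says.** The Background gives the purpose of phasing: "To control for secular trends, implementation of the intervention will be phased across the hospitals". The text with Fig. 1 adds: "Implementation of the intervention across four acute care hospitals will be staged, with multiple clusters in each of two implementation stages", and then names the level at which the control is formed: "The staged implementation of the intervention allows for a control between the two Health Districts".

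The analysis section for the point prevalence data plans to test "differences in the prevalence of IDCs between Health District 1 (post) and Health District 2 (no intervention". It also stratifies within-group data by ward and adjusts the between-group analyses for patient demographics that differ at baseline.

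Under Setting: "The intervention sites are four acute care hospitals from two Health Districts in NSW, Australia". Hospitals A and B belong to District 1, and C and D to District 2. "Hospitals have been purposively selected, matched on total bed numbers, activity type and activity levels"; no random allocation of the order is described. District 1 keeps paper records and District 2 electronic ones, with data collection adapted to each. The article also notes that "local clinical practice guidelines for urinary catheterisation for each Health District are available for all clinicians", and it allows some flexibility of delivery by district.

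The sample size section states 500 patients per Health District for a fall from 15% to 9%, with power 0.8 and alpha 0.05.

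**The concern.** The article's case for this design is that earlier hospital-wide studies were uncontrolled pre-post comparisons and so could not account for secular trends. The phased start is meant to repair that. A concurrent untreated district does so for any trend that acts on both districts.

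It does not do so for a change that acts on one district only. The two hospitals in a stage share a start date and a set of district-level influences, and the article itself names some: local guidelines, the record system with its own data collection method, and latitude in delivery. If one of these changes in one district between surveys, the resulting shift in catheter prevalence enters the controlled contrast together with the intervention effect. Ward strata and demographic adjustment act within a district or on patient mix, so neither removes it. A patient-level standard error does not contain this variation either, so a confidence interval built on it could be too narrow by an amount that the contrast cannot reveal.

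**Working it through.** **1. What is staged.** The text with Fig. 1 forms the control between districts, and the analysis section compares District 1 (post) with District 2 (no intervention). Both imply A+B first and C+D later. Fig. 1 itself is not reproduced in the text, so this reading rests on those two statements, which agree.

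**2. The plan's own figure.** Inputs: 15% v 9%, power 0.8, alpha 0.05 (two-sided assumed), 1:1.
- n = [1.960 × √(2 × 0.12 × 0.88) + 0.842 × √(0.15 × 0.85 + 0.09 × 0.91)]² / 0.06² = 459.3, so 460 per district.
- With continuity correction: (459.3/4) × [1 + √(1 + 4/(459.3 × 0.06))]² = 492.1, so 493.

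The stated 500 reproduces to within 3%. The formula has no district or hospital term, so the stated power and alpha hold only if patients are independent.

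**3. Units available.**
- Districts: 2 − 2 = 0 degrees of freedom for between-district variation; smallest two-sided permutation p = 2/2 = 1.
- Hospitals (2 v 2): 4 − 2 = 2 degrees of freedom; critical t 4.30 instead of 1.96; C(4,2) = 6 allocations, so the smallest two-sided permutation p = 2/6 = 1/3.

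**4. Size, under an assumption.** Let each district-by-survey prevalence carry an independent shift with SD τ. The documents give no τ; 0, 1 and 2 percentage points are shown. With the sample size section's estimated beds (610 and 860), 15% prevalence under the null and a baseline-netted contrast:
- Sampling variance V₀ = 2 × 0.15 × 0.85 × (1/610 + 1/860) = 7.15 × 10⁻⁴.
- True variance V = V₀ + 4τ².
- True type I error = 2 × [1 − Φ(1.96 × √(V₀/V))].

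| τ (points) | V | 1.96 × √(V₀/V) | True error |
|---|---|---|---|
| 0 | 7.15 × 10⁻⁴ | 1.96 | 5% |
| 1 | 11.15 × 10⁻⁴ | 1.57 | 11.7% |
| 2 | 23.15 × 10⁻⁴ | 1.09 | 27.6% |

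For a post-only contrast both V₀ and the added term halve (to 2τ²), so the rates are the same. With Table 1's 620 and 867 beds they are 11.7% and 27.8%.

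**5. What a hospital-level check buys.** Take four equal hospitals of (620 + 867)/4 = 371.75 patients and no hospital variation beyond sampling, on post-survey data.
- Sampling variance of the difference in district means = 0.1275/371.75 = 3.43 × 10⁻⁴.
- A district shift adds 2τ² to the numerator but nothing to the spread between hospitals of the same district. The effective cut-off falls from 4.30 to 4.30 × √(3.43/5.43) = 3.42 for τ = 1, and to 4.30 × √(3.43/11.43) = 2.36 for τ = 2.
- On t with 2 degrees of freedom the true error is about 8% and 14%, against 12% and 28% at patient level.

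The protection is partial, and power is low: about 0.49 for 15% v 9% on the same inputs.

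**The case against.** Several points on the other side are sound.

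- **The wording is not false.** Two hospitals per stage are literally several clusters, and phasing across hospitals is compatible with phasing by district. A reader might infer that these statements contradict each other; they do not.
- **Shared trends are removed.** That is a real gain over the uncontrolled studies the article cites.
- **District 2 crosses over later.** A reader might infer that the study holds no evidence at all on a district-specific change. That goes too far. A one-off shift in District 1 would not reproduce a fall in District 2 at its own, later start. This is partial replication: it is again one unit, with no untreated district alongside.
- **Staging by district is defensible.** A reader might infer that each stage should instead hold one hospital from each district, since Table 4 delivers training by facility ("1x 2-3 h workshop at each facility at start of intervention"). But the same table feeds prevalence back at ward, facility and district level, and guidelines are local to the district, so control hospitals would be exposed to contamination. Within-district contrasts would also leave two paired differences: 1 degree of freedom, critical t 12.7. Registration was retrospective, so the order may already be fixed. Restaging is a trade-off, and the documents do not make it a correction.
- **The size is assumed.** Nothing in the documents fixes the SD of a district shift, and at zero the nominal 5% holds. A reader might infer that the plan's error rate is shown to be wrong; it is shown only to depend on an unstated assumption.

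What stands is the identification problem, which does not depend on the assumed SD, and the fact that the hospital-by-hospital changes offer a check that the patient-level result lacks.

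**Conclusion.** The concern holds in a limited form. The controlled contrast has one Health District per stage. It controls trends common to both districts and cannot separate the intervention from a change confined to one of them, and more patients, wards or strata do not alter that. The stated alpha and power are correct as independent-patient arithmetic and assume no district or hospital variation. With independent district-by-survey shifts of SD 1 or 2 percentage points, the patient-level test's true false-positive rate would be about 12% or 28% instead of 5%. The matter bears on how firmly the controlled result can be stated. It does not show that the design is invalid or that the staging must change.

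**What to change.** Keep the staging, and make three changes.

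1. **Add a table** of the baseline-to-post change in catheter prevalence for hospitals A, B, C and D separately, with a hospital-level comparison (2 degrees of freedom, critical t 4.30; two-sided permutation floor 1/3) as a check on the patient-level result. Say beside it that the check captures hospital-level variation and only partly protects against a district-wide shift, and that with four hospitals a non-significant result there is not evidence of no effect. Show District 2's later change as partial replication without a concurrent control.
2. **Restate the claim** to control secular trends, wherever it appears, as control of trends common to both districts, assuming no district-specific change between surveys.
3. **Add to the sample size section** that the stated power and alpha assume no variation between districts or hospitals.

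The cost is one extra table, a few sentences and a less favourable statement of certainty. No sites, patients or surveys are added.

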### Setting

The intervention sites are four acute care hospitals from two Health Districts in NSW, Australia. Hospitals have been purposively selected, matched on total bed numbers, activity type and activity levels (See Table 1).

**Table 1 Tab1:** Setting

Health District	Facility	Beds
1	Hospital A	360
	Hospital B	260
	Total beds Health District 1 = 620	
2	Hospital C	549
	Hospital D	318
	Total beds Health District 2 = 867	

A key difference between the two health districts is the system used for medical health records: Health District 1 uses paper-based medical records, whereas Health District 2 uses electronic medical records. Data collection methods and training have been individualised to accommodate these differences.

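### Table 1 does not bear out the claimed matching on total bed numbers, and the between-district contrast has no planned control for ward type

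*Protocol article*

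**What the plan says.** The Setting section describes site selection in one sentence, "Hospitals have been purposively selected, matched on total bed numbers, activity type and activity levels", and points to Table 1. The table holds bed counts only. For Health District 1 it gives "Hospital A 360" and "Hospital B 260", with "Total beds Health District 1 = 620". For Health District 2 it gives "Hospital C 549" and 318 beds for Hospital D, with "Total beds Health District 2 = 867". It names no pairs, sets no tolerance, and shows nothing on activity type or level.

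The Design section gives the district comparison its role: "The staged implementation of the intervention allows for a control between the two Health Districts". The first comparison in the statistical analysis section sets District 1 after implementation against District 2 before it has received the intervention. On case mix, the same section says: "Within group data will be stratified according to wards to allow for variation in the case mix of patients between wards". For the between-group analyses it promises control for patient demographics if they are found to differ at baseline. Table 2 counts diagnosis and admission type among those demographics. The power section also mentions ward stratification, as a source of extra power, without saying to which comparison it applies.

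**The concern.** The article claims matching on bed numbers and cites, as support, a table whose figures do not show it. This would be a matter of wording if nothing depended on it. But the sites were chosen purposively, there are two hospitals per district, and District 2 serves as the untreated control. A reader judging whether that control is fair will give weight to a statement that the hospitals were matched.

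The analysis plan does not fill the gap by another route. It recognises that case mix varies between wards, but deals with this by stratification only within groups. In the between-district contrast, a difference in the share of wards where catheters are common could be mistaken for an intervention effect, or could hide one. The stated protection is adjustment for demographics, and it operates only if a baseline difference is detected.

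**Working it through.** **Inputs** (Setting, Table 1): A = 360, B = 260, C = 549, D = 318 beds; A and B are in District 1, C and D in District 2.

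**Step 1: reproduce the stated totals.** 360 + 260 = 620 and 549 + 318 = 867. Both agree with the table.

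**Step 2: compare the districts.** 867 − 620 = 247 beds; 867 / 620 = 1.40.

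**Step 3: try every complete pairing of four hospitals** (ratio = larger / smaller).

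| Pairing | First pair | Second pair |
|---|---|---|
| A–C and B–D | 549 − 360 = 189; ratio 1.53 | 318 − 260 = 58; ratio 1.22 |
| A–D and B–C | 360 − 318 = 42; ratio 1.13 | 549 − 260 = 289; ratio 2.11 |
| A–B and C–D (within district) | 360 − 260 = 100; ratio 1.38 | 549 − 318 = 231; ratio 1.73 |

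The worst pair in the three arrangements is 1.53, 2.11 and 1.73. Every complete pairing leaves at least one pair 1.5-fold or more apart. The bed claim fails by hospital pair and by district total.

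**Step 4: does the imbalance harm the sample size?** For 15% v 9%, two-sided alpha 0.05 and power 0.8, the usual two-proportion formula gives 460 per group, or 493 with continuity correction. The stated 500 per district is reproduced, and both districts have more beds than that. The bed imbalance does not undermine the sample size.

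**Step 5: set the two case-mix provisions side by side.**

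- Within groups: stratified by ward, with case mix given as the reason and no condition attached.
- Between groups: adjusted for demographics, only if a baseline difference is found, with ward type not mentioned.

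Within-group strata cannot simply be carried across. Each ward belongs to one hospital, so individual wards are not shared strata between districts. A shared stratum needs a ward-type code that means the same thing in all four hospitals, and the article defines none.

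**Step 6: how large could a ward-mix effect be?** The documents do not give ward shares, so any figure is an assumption. If high-use wards had 40% catheter prevalence and the rest 12%, and high-use wards made up 10% of beds in one district and 15% to 20% in the other, the crude difference would be (0.15 − 0.10) × (40 − 12) = 1.4 points to (0.20 − 0.10) × (40 − 12) = 2.8 points. With 31% for high-use wards (the orthopaedic figure in the Background section) it would be 0.05 × 19 = 0.95 to 0.10 × 19 = 1.9 points. The planning difference is 15 − 9 = 6 points. This shows only how the mechanism works. Nothing links a bed ratio of 1.40 to these ward shares, and the figures ignore the planned demographic adjustment.

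**The case against.** A reader might infer from Table 1 that District 2 is not a comparable control. The documents do not support that. Bed number is one of three stated criteria. Activity type and level bear more directly on catheter use, and the article gives no data on either, so non-comparability is neither shown nor refuted. The outcome is a proportion, and a larger denominator does not bias it. No tolerance or pairwise rule is stated, and one pair (A–D) is close. This objection stands, and it limits the point to the bed claim itself.

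A reader might also take matching to be the article's main argument for the control. It is not: the article relies on phased implementation, with baseline surveys and pre-post comparison in all hospitals. A stable difference in ward mix does not bias a within-hospital comparison, and a baseline difference in prevalence between districts would be visible. This stands too.

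Further, the between-district contrast is not left crude. Conditional control for demographics is planned, and because these include diagnosis and admission type it could capture part of the case mix. The power section's remark on ward stratification could be read as covering all comparisons. This stands in part. The adjustment depends on a difference being detected, it does not use ward type, and the analysis section, which is the more specific text, confines ward stratification to within-group data.

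Finally, an analysis plan that is not shown may hold detailed ward coding. That is why the absence of such detail is not the complaint. The complaint is that the article prints a claim its own table contradicts, and that it applies the ward case-mix provision to one comparison and not to the other.

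**Conclusion.** The point holds in a limited form. The statement of matching on total bed numbers is not supported by Table 1: the district totals differ 1.40-fold, and every complete pairing leaves at least one pair between 1.53-fold and 2.11-fold apart. This rests on arithmetic from the table and needs no assumption.

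What follows is that bed matching cannot be used as a reason to regard District 2 as a fair control. It does not follow that the districts are non-comparable, that the between-district estimate is biased, or that the study is underpowered. The size of any ward-mix effect cannot be derived from the bed ratio; the 1.4 to 2.8 points above depend wholly on assumed ward shares and prevalences.

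The practical weakness is that ward case mix is handled unconditionally within groups, while the between-group contrast has only demographic control triggered by a detected difference. With purposively selected sites and the bed matching not borne out, closing that gap is a cheap improvement.

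**What to change.** 1. In the Setting section, correct the wording on bed matching, or state its basis (which hospitals were paired and what difference was accepted). Report that the two districts differ 1.4-fold in beds. If matching on activity type and level is retained, give the data that show it.
2. Code each point prevalence record with a ward type defined in the same way for all four hospitals.
3. Adjust or stratify the between-district contrast by ward type, whether or not a baseline difference is detected, in addition to the planned adjustment for demographics.

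The cost is a change of wording, one extra data code and its definition. The small downside is that ward types found in only one district add nothing to the between-district contrast; they still contribute to the within-district comparisons.
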